## Results

Recruitment commenced on October 2, 2023. The study was completed with 34 participants recruited by May 2024, and all data were collected by August 2024. Currently, the data of the study are being analyzed and prepared for publication. The first publication of results is expected for summer 2025.

## Discussion

### Principal Findings

This feasibility study is expected to yield valuable insights to inform the design and methodology of a future definitive clinical trial evaluating the effectiveness of the aktivplan digital health intervention for regular physical activity following phase II rehabilitation. The initial implementation has already generated learnings to inform the study design. After 24 weeks, 34 (85%) participants were recruited, compared to the originally planned 40 participants, indicating that recruitment requires more time than initially anticipated. This observation supports the need for a broader, multicenter recruitment strategy in future clinical trials to ensure adequate sample size and generalizability. In addition, data on the usability, user experience, and acceptance of the aktivplan app will guide the need for further iteration before entering a definitive trial. Findings regarding the implementation in practice will inform future implementation strategies, including training for health care professionals, background technical support for health care professionals and patients, reimbursement strategies, and considerations to minimize barriers to implementation.

### Dissemination Plan

The results of this study will be published in peer-reviewed scientific journals. Due to the large volume of data generated, 3 manuscripts will report on 3 distinct aspects of the study: feasibility of the study design; usability, user experience, and acceptance of the aktivplan app; and preliminary clinical outcomes. In addition, the results will be presented at scientific conferences relevant to cardiac rehabilitation and digital technologies. A plain language summary for the cardiac community will be available on the sponsor’s website. Authorship will follow the International Committee of Medical Journal Editors authorship criteria. Professional medical writers will not be employed. It is not planned to make the participant-level dataset publicly available.

### Comparison to Prior Work

As mentioned before, the Austrian Health Interview Survey shows that only 48.1% of men and 45.1% of women aged between 18 and 64 years meet the WHO recommendation of endurance-type physical activity at moderate intensity and only 26% of men and 21.1% of women meet the WHO recommendations for both endurance-type physical activity and muscle-strengthening exercises [10]. Even after completing a cardiac rehabilitation program, 75.3% of patients in Austria fail to sustain sufficient physical activity in the long run [49]. Furthermore, as mentioned in the review of Meinhart et al [16], digital technology offers possibilities to successfully support physical activity following a cardiac rehabilitation program. Nevertheless, a recent survey by Lunz et al [50] revealed a relatively high motivation for using digital technology, but still low actual use (52%) of digital technology by health care professionals in the secondary prevention of CVD in Austria. Digital technology is mainly used for monitoring heart rate, with no established evidence-based digital health interventions for supporting physical activity habit formation [50]. Internationally, the systematic review of Luijk et al [17] describes moderate outcomes and heterogeneous quality of studies investigating the effectiveness of digital health interventions for maintaining physical activity in patients with CVD after phase II cardiac rehabilitation. However, the authors still recommend using digital health interventions in clinical practice until further evidence becomes available. Importantly, the transferability of digital health interventions between countries is often limited due to local sociocultural aspects (eg, language and representativeness of imagery) and particularities of clinical pathways and health care systems [51]. An example of the latter in Austria is the definition of 4 phases of cardiac rehabilitation, in contrast to the 3-phase model commonly used in other countries. The Austrian rehabilitation pathway offers the choice between inpatient or outpatient settings for phase II rehabilitation, and the duration and intensity of cardiac rehabilitation programs can differ to current models in other countries [3].

The aktivplan digital health intervention is therefore specifically developed for the Austrian rehabilitation pathway, and this feasibility study is deliberately conducted within the Austrian health care system to avoid variability introduced by cross-national differences in health care structures and cardiac rehabilitation programs.

### Strengths and Limitations

A strength of this study is the nature of the aktivplan intervention, which answers directly to an identified clinical need in the Austrian cardiac rehabilitation pathway, and which was developed specifically to match the cultural and systemic context in Austria using co-design methodology and patient involvement. This means that the aktivplan intervention has high clinical relevance and good sociocultural fit in the Austrian context. At the same time, this presents a limitation to the aktivplan intervention in terms of transferability to other international settings. A potential implementation of aktivplan in other countries would require an assessment of the intervention against national regulatory standards and requirements [52] and local clinical and sociocultural contexts. A further limitation to this study is the lack of blinding. Blinding of patients and health care professionals who are delivering the intervention is not possible in this case. Blinding of outcome assessors would be possible in principle; however, after early discussions with site principal investigators it was decided to conduct unblinded assessments. It was suggested that, because of the small number of available study staff and close working relationships at the study sites, blinding of assessors was not feasible, and the success of assessor blinding was unlikely. Finally, it is acknowledged that there are no prespecified criteria to judge whether, or how, to proceed with a future definitive trial [22]. Because no comparable previous studies are available for Austria, and prespecified criteria are not imposed by the funding organization, the decision whether, or how, to proceed with a future definitive trial will be made in discussion with relevant stakeholders and based on the data from this feasibility study and comparable international studies.

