**Methods:**

This multicenter, mixed method, randomized controlled pilot study aims to recruit 40 patients with an established diagnosis of CVD or with increased risk of CVD (physically inactive along with 1 further CVD risk factor) who are undergoing phase II rehabilitation at 2 rehabilitation centers in Austria. Participants will be allocated to the intervention or standard care control group by stratified randomization and will be monitored for 10 weeks after discharge from phase II rehabilitation. Participants, health care professionals, and outcome assessors are not masked (blinded) to group allocation. Data collection will include recruitment and drop-out rate; data completeness; adherence to the intervention; usability, user experience, and user acceptance questionnaires; technical reliability of the intervention; clinical assessments (exercise capacity, physical activity behavior, and CVD risk factors); adverse events; self-reported outcome measures (health-related quality of life, exercise self-efficacy, depression and anxiety, and kinesiophobia); patient interviews, and focus groups with health care professionals. Quantitative data will be analyzed descriptively, and 95% CIs will be calculated for recruitment and drop-out rates and for data completeness. No confirmatory inferential statistical analysis or hypothesis testing will be conducted. Qualitative data will be analyzed thematically by framework analysis.

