### Randomization

Participants will be individually randomized to the intervention or control group. Randomization will be stratified by study site, participant sex, and participant exercise capacity (peak power <1.3 Watts/kg, 1.3-1.8 Watts/kg, and >1.8 Watts/kg in incremental cycle ergometry). The randomization schedule will be prepared in advance by the study statistician who is not involved in participant recruitment. The *blockrand* package of the statistical program R (R Foundation for Statistical Computing) will be used [29]. The package enables the randomized allocation of participants for clinical and experimental studies in which participants are recruited individually and sequentially. The randomization schedule will be stored securely at the study sponsor’s office (Ludwig Boltzmann Institute for Digital Health and Prevention), which is at a different location to the study sites. Random allocation is concealed, as personnel at the study sites have no access to the randomization schedule. After a new study participant has been recruited, the site principal investigator informs the study sponsor of the patient’s sex and exercise capacity, and the randomization result is then returned to the site principal investigator.

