### Description of the Intervention

The aktivplan digital health intervention was developed at the Ludwig Boltzmann Institute for Digital Health and Prevention, Austria, in a human-centered process with both co-design and iterative participatory design elements, involving health care professionals and patients with cardiac problems between 2020 and 2022 [30]. The core feature of the aktivplan app is a digital calendar for planning regular heart-healthy physical activity. Health care professionals access this calendar via a website or web app (view for health care professionals), and patients access the calendar via an app on their smartphone, tablet, or—if required—via a website on a smartphone, tablet, or computer (view for patients). Before discharge from the phase II rehabilitation program, the aktivplan app is introduced to the patient in a 1:1 consultation with a health care professional experienced in exercise prescription (eg, physiotherapist, sports scientist, and exercise physiologist). This consultation is conducted according to the principles of shared decision-making [31]. A personalized heart-healthy physical activity plan is agreed upon, which the patient should carry out independently following discharge from the phase II rehabilitation program. The health care professional enters this training plan into the aktivplan calendar. Using the aktivplan app, the patient can view their planned physical activity sessions, mark sessions as completed, or enter additional unplanned physical activities (eg, spontaneous activities that are self-initiated by the patient). The health care professional can view the calendars and assess adherence with personal physical activity plans for all patients under their care.

In addition to this core functionality, the aktivplan digital health intervention includes further distinct features, such as automated messages to the patient with motivational content or reminders of planned physical activity sessions, personalized goal setting, and the option for the health care professional to give the patient feedback and contact them via an in-app message. Further details on the aktivplan digital health intervention are given in the TIDieR checklist in Multimedia Appendix 3. Details of the logic model and psychological and behavior change theory underpinning the aktivplan digital health intervention have been published previously [19].

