Secondary outcomes.Exercise capacity (highest mechanical power output achieved during incremental cycle ergometry, peak power)Physical activity behavior (accelerometry and daily minutes of moderate to vigorous physical activity)Body massArterial blood pressureBlood cholesterol levelsGlycated hemoglobin levelsSmoking (number and type of smoking products per week)Health-related quality of life (EQ-5D-5L questionnaire)Exercise self-efficacy (Exercise Self-Efficacy Scale)Depression and anxiety (Patient Health Questionnaire-4)Kinesiophobia (selected items from the Tampa Scale of Kinesiophobia)Patient safety (adverse events reporting according to regulatory standards: number, type, and severity of adverse events)

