### Data Management

At the study sites, data will be recorded on paper-based case report forms (CRFs). Following completion of data collection, the CRFs and electronic data collection devices (wearables, dictaphones, and video cameras) will be collated and securely stored at the study sponsor site. Data from CRFs will be entered onto a Microsoft Excel file. Quality of data entry will be assessed by independently cross-checking the accuracy of 10% of data cells. After completion of the analysis, study data will be securely archived by the sponsor for 10 years.

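### Assessor masking is waived for every outcome, but the reason given covers only site-conducted assessments and leaves the scoring of accelerometry open to being unmasked

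*Protocol article*

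**What the plan says.** The Methods paragraph of the abstract makes no exception by outcome: "Participants, health care professionals, and outcome assessors are not masked (blinded) to group allocation". Strengths and Limitations repeats the position. It concedes that "Blinding of outcome assessors would be possible in principle", reports that "after early discussions with site principal investigators it was decided to conduct unblinded assessments", and gives one ground for not masking: "because of the small number of available study staff and close working relationships at the study sites, blinding of assessors was not feasible". It adds that masking was unlikely to succeed. It names lack of blinding as a limitation but does not separate outcomes measured by site staff from outcomes computed from a device.

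The secondary outcomes include "Physical activity behavior (accelerometry and daily minutes of moderate to vigorous physical activity". Under Physical Activity and Heart Rate Measurements, participants in both groups receive a wrist accelerometer and a heart rate sensor by post, wear them during waking hours in weeks 8 to 10, and return them at the final visit. Data Management then says that "electronic data collection devices (wearables, dictaphones, and video cameras) will be collated and securely stored at the study sponsor site".

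Two further statements concern the sponsor. Under Randomization, "The randomization schedule will be stored securely at the study sponsor" (its office, which is at a different location from the sites). Under Description of the Intervention, the app "was developed at the Ludwig Boltzmann Institute for Digital Health and Prevention, Austria", which is the institute that the Randomization section identifies as the sponsor.

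**The concern.** The waiver is wider than its justification. Few staff and close relationships at a rehabilitation centre explain why a site assessor who runs an ergometry test is likely to know the patient's group. They do not explain why whoever turns accelerometer files into daily minutes should know it. For a device outcome, the person who scores the file is in effect the assessor, and that step can be masked whatever is known at the sites.

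Accelerometry is a direct measure of the behaviour the intervention targets, and one of the few clinical outcomes here whose scoring could be masked at almost no cost. The secondary aim is to collect clinical outcomes that inform the sample size of a definitive trial, and the Analyses section plans a group comparison of them with 95% CIs. Scoring that is protected from knowledge of allocation would make that one outcome easier to trust when the others are unmasked.

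**Working it through.** The point rests on text, so the check sets the sections side by side.

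**1. Scope of the waiver.** The abstract says outcome assessors are not masked, with no outcome excepted. Strengths and Limitations speaks of unblinded assessments, again with no exception.

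**2. Scope of the reason.** The reason came from discussions with site principal investigators and concerns staff and relationships at the sites.

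**3. The reason applied to each kind of outcome.**

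| Outcome | How it arises in the article | Does the site reason apply? |
|---|---|---|
| Peak power, body mass, blood pressure | Routine assessments and clinical records | Yes |
| Questionnaires | Completed by participants, who are unmasked | Assessor masking is not the issue |
| Daily minutes of moderate to vigorous activity | Device worn at home, then collated at the sponsor | No |

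**4. Conditions at the sponsor.** Three facts meet in one organisation: it receives the devices (Data Management), it holds the schedule and returns each allocation to the site (Randomization), and it developed the app (Description of the Intervention). An ordinary study ID could therefore be linked to a group there.

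**5. What is not stated.** The article does not name who derives the activity minutes, and does not say whether that person knows the allocation. Custody of devices and list by one organisation makes unmasked derivation possible. It does not establish it.

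**6. Figures.** The plan gives no figure that bears on masking. Its one design figure, 40 patients to detect a problem of 7.5% prevalence with 95% confidence, reproduces: ln(0.05)/ln(0.925) = 38.4, rounded up to 39, and with 40 patients the probability of at least one occurrence is 1 − 0.925^40 = 95.6%. Masked derivation would leave this, and every planned interval, unchanged.

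**The case against.** The strongest reply is that the statement and its reason have the same scope. On this reading, outcome assessors means the people who conduct assessments at the sites, and nothing is said about data processors because nothing was decided about them. Coded processing, wear-time rules and intensity cut-points commonly stand in an SAP or full protocol that is not shown, so their absence is not a fault. Lack of blinding is also disclosed, and the outcome is secondary and exploratory.

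Much of this stands. The absence of wear-time and cut-point rules is not part of this point. Disclosure and the exploratory purpose limit severity. What remains is that the text waives masking without exception and defends the waiver with a reason that does not reach one listed outcome. If the narrow scope was intended, one sentence would say so.

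A reader might infer three stronger things, none of which the documents support.

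- **That the sponsor scores accelerometry unmasked.** No section says so. The schedule was prepared by a statistician not involved in recruitment and is stored securely. Possession of the list by an organisation does not show that the person processing files uses it.
- **That the bias can be sized.** As pure illustration, take 17 analysable participants per arm. The SE of a standardised difference is √(2/17) = 0.343 SD. If the most favourable of four processing rules were kept, with estimates correlated at 0.9 or 0.8, the expected upward bias would be 1.03 × √(1 − 0.9) × 0.343 = 0.11 SD or 1.03 × √(1 − 0.8) × 0.343 = 0.16 SD (1.03 being the expected maximum of four standard normals). The article gives 34 recruited in total, with no split by arm and no drop-out count. The number of rules, the correlation and the deliberate selection are all invented for the example. Fixing the rules in advance would remove this selection even without masking, so the figure does not measure harm from unmasked assessment.
- **That a biased difference would feed the definitive sample size.** The article says clinical outcomes will inform that calculation, but not that the observed group difference will. If only the SD is used, a bias in the difference does not carry over. Nor does the article rank accelerometry as the future primary endpoint.

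**Conclusion.** The concern holds in a limited form. The waiver is unrestricted, its only stated reason is bound to the sites, and accelerometer-derived activity falls outside that reason. Derivation of this outcome is therefore open to being unmasked, at an organisation that also holds the schedule and developed the app. Whether it is in fact unmasked cannot be told from the article, and a full protocol or SAP may already provide for masked processing.

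This is a low-severity, cheap improvement. It concerns one of twelve secondary outcomes in a pilot without hypothesis testing, and no primary outcome is affected. No size of bias can be derived from the documents. Masked processing would protect only the scoring step: participants know their group, so differences in behaviour or in wear compliance between groups would remain.

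**What to change.** 1. In the abstract's Methods paragraph and in Strengths and Limitations, limit the statement on unmasked assessment to assessments conducted at the sites.
2. State that accelerometer and heart rate files are processed under recoded IDs that carry no allocation, and that derivation is completed before allocation is merged.
3. The article reports that data collection was complete and analysis under way. Where derivation is not finished, this order can still be followed. Where it is finished, report whether it was masked. If masked processing is already in place, one sentence saying so settles the point.

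The cost is recoding the files and fixing the order of the merge. No patient procedure, site staff or sample size changes.

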### Conclusions

There is a need for evidence-based interventions to support regular physical activity after discharge from phase II rehabilitation for patients with CVD or at risk of CVD. This pilot study is expected to generate valuable and comprehensive insights to inform the study design of a future definitive effectiveness trial of the aktivplan digital health intervention, guide the need for further iteration of the aktivplan app before entering a definitive trial, and inform future implementation strategies for the intervention.

## Appendix

Multimedia Appendix 1 SPIRIT checklist.

Multimedia Appendix 2 CONSORT (Consolidated Standards of Reporting Trials) checklist.

Multimedia Appendix 3 TIDieR (Template for Intervention Description and Replication) checklist.

Multimedia Appendix 4 Qualitative interview schedule.

Multimedia Appendix 5 Focus group topic guide.

## Abbreviations

BCT: behavior change technique
CONSORT: Consolidated Standards of Reporting Trials
CRF: case report form
CVD: cardiovascular disease
SPIRIT: Standard Protocol Items: Recommendations for Interventional Trials
TIDieR: Template for Intervention Description and Replication
WHO: World Health Organization
